### Participant timeline

The schedule of events is described in Table 3.

**Table 3 Tab3:** Timeline for study participants

Schedule of events			
	Day 0 visit	Day 7 visit (+/− 2 days)	Unscheduled visit
Informed consent and enrolment	x		
Demographic data collection	x		
History/physical examination	x	x	x
Diagnostic tests	x		
Treatment prescription	x		x
Patient adherence evaluation		x	x
Collection of qualitative data	x	x	
Delivery of communication messages	x		
Adverse event monitoring (see Safety reporting section)		x	x

### Sample size estimation

The sample size calculations were based on criteria that would allow evaluation of antibiotic prescribing at each site.

The sample size was calculated for each country in order to detect a 30% difference (with a 95% confidence interval of +/− 5%) in the antibiotic prescription proportions compared with the initial proportion without the intervention, with a power of at least 80% to detect such a precision estimate (Fig. 3). The minimal theoretical sample size obtained for each site [20] has been increased by 10% to allow for loss to follow-up.

**Fig. 3 Fig3:**
[figure not shown]
Sample size chart

Estimates of the current proportion of patients prescribed antibiotics for acute febrile illnesses at different clinics in each country study were used as the basis to calculate the required sample size (Table 4).

**Table 4 Tab4:** Baseline antibiotic prescription rates for acute febrile illnesses

Country	Expected antibiotic prescription rate in control arm (based on historic prescribing)	Reduction in prescribing	*N* per arm for children/adolescents	*N* per arm for adults	Total sample size (both arms, including losses to follow-up)
Nepal	55%	30%	1760	1760	3520
Uganda	73%	30%	1200 (combined)		2400
Ghana	43%	30%	1383	n/a	2766
Burkina Faso	77%	30%	859	n/a	1718
Myanmar	43%	30%	440	440	1760
India JSS	50%	30%	864	n/a	1728
India PGIMER	50%	30%	864	864	3456
India RD Gardi	20% (children), 40% (adults)	30%	553	831	2768
India NICED	50%	30%	880	n/a	1760
Total					21,876

Sample sizes are considered a minimum. Enrolment will continue after the sample size has been reached, through the 12 months of the intervention, to allow for seasonal variations.

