**Methods:**

We designed a randomized, controlled clinical trial to evaluate the impact of our intervention package on clinical outcomes and antibiotic prescription rates in acute febrile illnesses. Available, point-of-care, pathogen-specific and non-pathogen specific (host markers), rapid diagnostic tests (RDTs) included in the intervention package were selected based on pre-defined criteria. Nine clinical study sites in six countries (Burkina Faso, Ghana, India, Myanmar, Nepal and Uganda), which represent heterogeneous outpatient care settings, were selected. We considered the expected seasonal variations in the incidence of acute febrile illnesses across all the sites by ensuring a recruitment period of 12 months. A master protocol was developed and adapted for country-specific ethical submissions. Diagnostic algorithms and choice of RDTs acknowledged current data on aetiologies of acute febrile illnesses in each country. We included a qualitative evaluation of drivers and/or deterrents of uptake of new diagnostics and antibiotic use for acute febrile illnesses. Sample size estimations were based on historical site data of antibiotic prescription practices for malarial and non-malarial acute fevers. Overall, 9 semi-independent studies will enrol a minimum of 21,876 patients and an aggregate data meta-analysis will be conducted on completion.

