### Assignment of interventions

Enrolled patients will be randomized into either the intervention or the control arm. Patients in the intervention arm will be managed with a package of interventions (as detailed above) and patients in the control arm will be managed as per routine clinical practice.

Patients will be randomized centrally, by site, into the intervention or control arm in a 1:1 allocation ratio. Randomization codes will be prepared by the trial data manager based on the sample size estimates for each site and will be sent prior to commencement of enrolment to each site.

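### Table 4, Nepal row: the per-arm sizes imply 7,040 patients but the stated total is 3,520, so the row and the published minimum of 21,876 need reconciling

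*Protocol article*

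**What the plan says.** Table 4, under Sample size estimation in the protocol article, has two per-arm columns, one for children/adolescents and one for adults. A final column is headed "Total sample size (both arms, including losses to follow-up". The Nepal row is "Nepal 55% 30% 1760 1760 3520".

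Other statements bear on how that row should be read:

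- Assignment of interventions: patients are randomized centrally, by site, "into the intervention or control arm in a 1:1 allocation ratio", and the codes are prepared from each site's sample size estimate and sent out before enrolment begins.
- Sample size estimation: the theoretical size for each site "has been increased by 10% to allow for loss to follow-up". The aim is to "detect a 30% difference (with a 95% confidence interval of +/− 5%) in the antibiotic prescription proportions", with at least 80% power.
- The text after Table 4: the sizes are minimums, and recruitment goes on through the 12-month intervention period once they are reached.
- Abstract, Methods: "9 semi-independent studies will enrol a minimum of 21,876 patients". The same total closes Table 4.

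**The concern.** With two arms, 1:1 allocation and separate per-arm sizes for two age groups, a site total must equal twice the sum of the two per-arm entries. Nepal's does not; it is out by a factor of two.

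The article describes the trial as principally a site-level study with each site sized on its own, so a site's target should be readable from its row. Nepal also has the largest total in the table, whether 3,520 or 7,040. As printed, a reader cannot tell whether the Nepal minimum is 3,520 or 7,040, how long the Nepal randomization list should be, or whether the published trial minimum agrees with the sizes from which it was built.

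**Working it through.** **Inputs.** All per-arm sizes, totals and baseline rates are from Table 4. The two arms and 1:1 ratio are from Assignment of interventions. The 10% allowance and the ±5% precision are from Sample size estimation.

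**Step 1: row totals.** Formula: total = 2 × (children/adolescents per arm + adults per arm).

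| Row | 2 × (sum per arm) | Printed total | Agree |
|---|---|---|---|
| Nepal | 2 × (1760 + 1760) = 7040 | 3520 | no |
| Uganda (combined) | 2 × 1200 = 2400 | 2400 | yes |
| Ghana | 2 × 1383 = 2766 | 2766 | yes |
| Burkina Faso | 2 × 859 = 1718 | 1718 | yes |
| Myanmar | 2 × (440 + 440) = 1760 | 1760 | yes |
| India JSS | 2 × 864 = 1728 | 1728 | yes |
| India PGIMER | 2 × (864 + 864) = 3456 | 3456 | yes |
| India RD Gardi | 2 × (553 + 831) = 2768 | 2768 | yes |
| India NICED | 2 × 880 = 1760 | 1760 | yes |

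**Step 2: trial total.** The printed totals sum to 3520 + 2400 + 2766 + 1718 + 1760 + 1728 + 3456 + 2768 + 1760 = 21,876, which reproduces the article's figure. With Nepal at 7,040 the sum is 21,876 − 3,520 + 7,040 = 25,396. The difference is 3,520, and 3,520 / 21,876 = 16%.

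**Step 3: can loss to follow-up explain it?** No. No other row is inflated between the per-arm columns and the total, and an allowance for losses would raise a total, not halve it.

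**Step 4: which entry is likelier to be wrong?** A 30% relative reduction from 55% gives 0.7 × 55% = 38.5%. The variance term is 0.55 × 0.45 + 0.385 × 0.615 = 0.4843.

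- Reading ±5% as a 95% half-width of 5 percentage points on the difference between arms within one age group, n = 0.4843 × (1.96 / 0.05)² = 745 per arm. With the 10% allowance this is 820 (745 × 1.1) to 828 (745 / 0.9), about 6% below 880.
- Half-width at n = 880: 1.96 × √(0.4843 / 880) = 4.6 points. With 880 / 1.1 = 800 analysed it is 4.8 points. Both are within 5.
- Adding 80% power to detect a 5-point difference, n = 0.4843 × ((1.96 + 0.84) / 0.05)² ≈ 1,521 per arm. With the allowance this is 1,674 to 1,690, about 4–5% below 1,760.

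So 880 fits the precision reading and sits close to the 864–880 per arm used at the sites with a 50% baseline. But 1,760 is about as close to the second formula, and neither figure is reproduced exactly.

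**Step 5: power.** A plain comparison of 55% with 38.5% (two-sided 5%, 80% power) needs about 143 per arm. At 880 per arm the power is above 99.9%, and higher still at 1,760.

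**The case against.** The strongest reply is that the trial total is not miscalculated. 21,876 is the exact sum of the printed totals and agrees with the abstract, so if 3,520 is right the slip is confined to two cells. That stands: the total conflicts with the per-arm columns only through Nepal.

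A reader might infer that Nepal would stop at half its intended size or recruit twice its total. The article does not support this. The sizes are minimums and enrolment continues for 12 months after they are reached, so no Table 4 figure is a stopping point.

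The randomization argument can also be discounted in part. Randomization is by site, with no age stratification stated, so the natural input is the site total, which is printed as 3,520. Still, the codes are to rest on the site's sample size estimate, and for Nepal the table implies two.

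A reader might equally conclude that 880 + 880 is proved. It is not. A single 1,760 per arm covering both age groups, as in Uganda's row, also gives 3,520. Uganda's figure is marked as combined whereas Nepal's row carries a number under each heading, which counts somewhat against that reading without excluding it. Nor does meeting ±5 points identify 880, because Table 4 follows no single recoverable formula. Myanmar's 440 per age group at 43% gives 1.96 × √((0.43 × 0.57 + 0.301 × 0.699) / 440) = 6.3 points, while Ghana has 1,383 per arm at the same rate.

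**Conclusion.** The Nepal row contradicts itself by a factor of two: 7,040 from the per-arm entries against 3,520 stated. The same gap of 3,520 patients separates the published minimum of 21,876 from the 25,396 that the per-arm columns imply. This rests only on the column labels, two arms and 1:1 allocation, and the other eight rows confirm that reading of the labels.

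Which entry is wrong is a separate question that the article does not answer. A total of 3,520 with 880 per arm in each age group is the likelier reading; that judgement assumes ±5% means percentage points on the between-arm difference within an age group. It would be wrong to take the row as showing that 7,040 was intended, or that Nepal is underpowered. Power for the 30% relative reduction is ample on every reading. What is affected is the stated enrolment target, the Nepal randomization list and the consistency of the published total. It should be corrected because a stated sample size cannot carry two values.

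**What to change.** Check the source calculation for Nepal and reconcile the row.

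- **If 3,520 is right:** restate the per-arm entries, most likely as 880 children/adolescents and 880 adults (2 × (880 + 880) = 3,520), or as a single 1,760 marked as combined, in the way Uganda's row is. Leave 21,876 unchanged.
- **If 1,760 per arm in each age group is intended:** restate the Nepal total as 7,040 and the trial minimum as 25,396, in Table 4 and in the abstract.

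Base the Nepal randomization list on the reconciled figure, and confirm its length if it has already been prepared.

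The cost is one table row and no extra patients if 3,520 stands. If 7,040 was intended, the stated minimum rises by 3,520.

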### Strategies for achieving adequate participation enrolment

We estimate, based upon clinic registries for the previous 1 or 2 years, that there will be adequate enrolment of participants in all of the sites.

### Assignment of interventions

Enrolled patients will be randomized into either the intervention or the control arm. Patients in the intervention arm will be managed with a package of interventions (as detailed above) and patients in the control arm will be managed as per routine clinical practice.

Patients will be randomized centrally, by site, into the intervention or control arm in a 1:1 allocation ratio. Randomization codes will be prepared by the trial data manager based on the sample size estimates for each site and will be sent prior to commencement of enrolment to each site.

### Blinding and masking

Not applicable as this is an open label study.

### Data management

All anonymized clinical participant data relating to the trial will be recorded in electronic CRFs created on the study sponsor’s online clinical trials platform (OpenClinica Enterprise Edition *version 4.0*). The sponsor will provide training on CRF completion prior to the start of the study. Electronic data capture (EDC) will be performed via eCRFs on android tablets in offline mode, to facilitate data entry at peripheral sites with limited internet connections, and synchronized daily at site research offices with verified, reliable internet connections. Paper CRFs will be available as back-up. Only authorized study personnel will have access to the CRFs. Consent forms containing patient identifying data will be retained at each site and kept in secure lockable cabinets in a secure room with restricted access.

Records and documents, including signed informed consent forms (ICF) pertaining to the conduct of this trial will be retained by the principal investigator for 10 years after trial completion, unless local regulations or institutional policies require a longer retention period.

### Data quality

Training on the protocol, Good Clinical Practice (GCP), Good Clinical Laboratory Practice (GCLP) and the use of the diagnostic tests will be provided by the sponsor and University of Oxford. A laboratory manual, which describes all of the sample testing procedures, will be provided by FIND prior to the commencement of the trial. Detailed training on the EDC system will be provided by the data manager prior to first participant enrolment at each site. All of the POCT results will be photographed following a standard operating procedure. These photographs will be uploaded into the CRF to ensure the quality of the POCT data being recorded in the database and so that corrective procedures can be followed should there be any discrepancies between the laboratory staff and the monitor, since a patient’s ongoing care is based on these results. The sponsor will perform risk-based monitoring of this trial, and associated quality control checks in line with ICH GCP, and all applicable regulatory requirements.

Training on qualitative methods of data collection, analysis and use of the behaviour change wheel [21] process will be provided by the University of Oxford and/or onsite social science leads.

### Statistical methods

We have a dedicated SAP that is currently under review that will cover the statistical analysis in great detail, focusing not only on the country-specific analyses, but also on the overall analysis from the combination of the data from all countries. We foresee the analysis to need some country-specific adjustments. However, here is an overview of the analyses we will perform.

### Populations for statistical analyses

Table 5 describes the study populations for the purposes of analyses.

**Table 5 Tab5:** Populations for statistical analyses

Population	Description
1. Enrolled	All participants who sign the ICF
2. Randomly assigned to trial intervention (RAI)	Randomized to either intervention or control arm
3. Modified intent to treat (mITT)	Participants in RAI with partial data (but not fully compliant with the protocol)
4. Evaluable per protocol population (PP)	All participants who fully complied with the protocol
5. Safety population for analysis	All participants randomly assigned to trial intervention. Participants will be analysed according to the intervention they actually received.

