### Study design

The study design captures a wide range of qualitative contextual outcomes and quantitative empirical outcomes in order to address the various aspects of the core research question.

Overall, this is a prospective, comparative, multicountry and multisite, open-label, two-armed, 1:1, randomized-controlled trial which will compare the impact of the intervention package (POCTs, clinical algorithm, clinic process flow, and training and communication) on clinical outcomes and antibiotic prescription patterns in febrile patients with the current practice. All sites have adopted a common protocol that reflects differences in patterns of infection and behaviours at each site and in each geographical area.

As this is principally a site-level study, sample sizes have been generated to provide the required statistical power for each individual site. Analyses will be conducted at two levels: first at the site level on individually randomized study participants, and secondly, on the combined studies as an aggregated-data meta-analysis across all sites, with the site as the unit of analysis.

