### Handling of missing data

Missing and invalid data for key measures that contribute to the evaluation of each of the outcomes will be reported in summary tables and will not be imputed. The primary outcomes do not involve quantitative assessments, and therefore, we feel it would not be appropriate to input data. Data from participants for whom partial data are available will be included in the analysis of specific outcomes, provided the data allow to evaluate them (e.g. adherence to prescription).

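### As printed, Table 5's modified intention-to-treat set contains no fully compliant participant, and the two primary endpoints name only that set and the per-protocol set

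*Protocol article*

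**What the plan says.** Allocation is individual, by site, "into the intervention or control arm in a 1:1 allocation ratio" (Assignment of interventions).

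Table 5 (Populations for statistical analyses) then defines the sets that matter here:

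- RAI, the all-randomised set: "Randomized to either intervention or control arm".
- mITT: "Participants in RAI with partial data (but not fully compliant with the protocol".
- PP: "All participants who fully complied with the protocol".
- Safety: everyone randomised, but "Participants will be analysed according to the intervention they actually received".

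Analysis of endpoints takes the favourable-outcome proportion and the antibiotic prescription rate, which are the two primary outcomes, in mITT and PP. It does not mention RAI. Handling of missing data rules out imputation and adds: "Data from participants for whom partial data are available will be included in the analysis of specific outcomes", where the data permit the outcome to be evaluated.

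**The concern.** A modified intention-to-treat set normally starts from everyone randomised and drops only those for whom the endpoint cannot be assessed. The printed row instead makes incomplete compliance part of the definition. An analyst who programs Table 5 literally would build one set of non-compliant participants and one of compliant participants, and would compare arms within each. Neither comparison is the randomised one.

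The selection need not balance out between arms. Only the intervention arm has a diagnostic algorithm to follow and an adherence message to receive; controls have routine care. The article also says that algorithm adherence will be judged from the case report forms, using test use and antibiotic prescriptions. If full compliance includes algorithm adherence, an off-algorithm antibiotic prescription would remove an intervention patient from PP, and that set would be selected partly on the endpoint itself.

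Both primary endpoints at all nine sites are affected, and so is the aggregated-data meta-analysis built on the site results.

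**Working it through.** The document states no figure to reproduce, so the check is on set membership, followed by an illustration with assumed rates.

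**Step 1. Place each randomised participant using the printed rows.**

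| Data | Fully compliant? | Literal mITT | PP |
|---|---|---|---|
| Complete | Yes | No | Yes |
| Complete | No | No (data are not partial) | No |
| Partial | No | Yes | No |
| Partial | Yes (if this can occur) | No | Yes |

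No row is in both sets, and one row is in neither. Literal mITT is therefore not even the complement of PP: participants with complete data who deviated drop out of both primary-endpoint analyses.

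**Step 2. Look for a place that restores the randomised comparison.**

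- Analysis of endpoints: mITT and PP only for the two primary endpoints. The inappropriate-prescription proportion and the proportion of compliant cases with a favourable outcome are in PP only. The last item, prescription by outcome, names no population.
- Efficacy analyses: between-arm estimates for both outcomes, with no population named.
- Safety population: all randomised, but grouped by intervention received, so it is no substitute for an as-assigned comparison.
- Handling of missing data: keeps partial-data participants where evaluable, but deals with missingness, not compliance.

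None of these redefines mITT or assigns RAI to an efficacy endpoint.

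**Step 3. See whether the direction of bias can be derived.** The article gives no compliance rate and no prescription rate by compliance. Assume, for illustration only: a control rate of 50% in every subset (Table 4 expects 50% at three of the Indian sites); 80% of intervention patients compliant, with an antibiotic rate of 30%; the other 20% with a rate of x, all falling in literal mITT.

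- All randomised, intervention arm: 0.8 × 30% + 0.2 × x
- Literal mITT, intervention arm: x
- PP, intervention arm: 30%

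| x | All randomised vs 50% | Literal mITT vs 50% | PP vs 50% |
|---|---|---|---|
| 45% | 24 + 9 = 33%, difference -17 points | -5 points | -20 points |
| 50% | 24 + 10 = 34%, difference -16 points | 0 points | -20 points |
| 55% | 24 + 11 = 35%, difference -15 points | +5 points | -20 points |

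The all-randomised difference hardly moves. The literal mITT difference goes from a reduction to an increase on the choice of x alone, and PP overstates the reduction throughout. If compliance were unrelated to prescribing and similar in both arms, the bias would vanish. The document does not say which of these cases applies.

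**The case against.** The strongest reply is that nobody means this. The row is labelled modified intention to treat. The missing-data section speaks of including people with partial data, which is the language of adding them to the complete cases. Other analyses calculates a figure within each arm that combines compliant and non-compliant participants, which needs a population holding both. Study design places the site analysis "first at the site level on individually randomized study participants". The likely intention was to include participants with partial data even if not fully compliant.

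That stands as a reading of intent. A reader might infer that the trial plans to analyse only protocol violators, and the document does not support that. It does not correct the row either. It already contrasts compliant with non-compliant participants elsewhere, so the literal set would not strike an analyst as absurd.

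Three further limits stand:

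- A reader might infer that no all-randomised comparison will be made at all. That is too strong, since Efficacy analyses names no population. What holds is that none is named for the primary endpoints.
- Full compliance is not defined. It could turn on day 7 attendance or sample provision, which apply to both arms, and *compliant* may sometimes mean adherence to the prescription. Differential selection by arm is possible, not established.
- A reader might infer that a reversed sign is to be expected. It appears above only when x is set higher than the control rate.

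The article also says that a SAP under review will give the detail. That would answer an omission. Here the article itself states a definition and applies it to the primary endpoints.

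**Conclusion.** The mITT definition is wrong as printed. Taken literally, it contains no fully compliant participant and does not overlap with PP, it leaves complete-data deviators in neither set, and the two primary endpoints name no other population. Both named sets then condition on compliance after randomisation.

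This is most plausibly a drafting error in one row, not a plan to discard compliant patients. It matters because it governs both primary endpoints and nothing else in the document overrides it. The set logic rests on the printed wording alone. The size and direction of the resulting bias cannot be derived from the document; the figures above are assumptions that show why.

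**What to change.** - **Table 5, mITT row:** define the set as all randomised participants with the endpoint in question observed, analysed in the arm assigned, regardless of compliance. PP is then a subset.
- **Analysis of endpoints:** state that this set is the primary population for the between-arm comparison of both primary endpoints, with PP reported alongside as supportive. Reporting both remains sensible, given the aim of not worsening clinical outcomes.
- **SAP:** carry the same wording.

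The new set still depends on the endpoint being observed, so missing day 7 outcomes should continue to be tabulated as the article plans. Table 3 schedules prescription at day 0, which should help completeness for the antibiotic endpoint. It also allows prescription at unscheduled visits, and the article does not say how complete these data will be.

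The cost is one table row and one sentence. No new data and no change to the sample size are needed.

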### Study outcomes

The primary outcome measures are the point estimates of:
The proportion of cases of acute febrile illness with favourable outcome (defined as being alive + no fever + resolution of day 0 symptoms) on day 7, in both arms.The proportion of antibiotic prescriptions for acute febrile illness in the two arms. Specifically, the study intends to detect a reduction (at least 30% from the baseline) in unnecessary antibiotic prescribing, without adversely affecting clinical outcomes. While antibiotic prescription rates are known at the study sites, outcomes are not currently known because patients are not routinely followed-up.

The secondary outcomes are:
Proportion of patients prescribed antibiotics at clinics who describe adherence to prescription on day 7.Proportion of healthcare workers who adhered to new algorithm.Proportion of participants experiencing adverse events (see description in Safety reporting section).

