### Data and safety monitoring board

Given that the clinical decision to prescribe or not prescribe antibiotics in the intervention arm of the study will be guided by the intervention package, there is a possibility that the diagnostic algorithm may fail to detect a need for antibiotics in some participants, thereby exposing them to the risk of getting worse from disease. It is also possible that routine procedures might expose patients to risks, such as those related to inappropriate use of antibiotics or missed diagnosis, which we will monitor, but we will not change the routine care for the patients in the control arm during the trial.

Therefore, we have established a data safety monitoring board (DSMB), composed of experts, many of whom are based in LMICs with experience in paediatrics, tropical infectious diseases, statistics, clinical trials and social science work.

The DSMB will evaluate ongoing safety data, assess the risks and benefits and give recommendations on whether to continue, amend or stop the trial. The DSMB will review, at agreed intervals, the following data as they relate to the study progress and participant safety:
Number of screened patients, by study siteNumber of included patients, by study site and by study armPatients’ baseline characteristicsNumber of patients withdrawn and lost to follow-up, by study site and by study arm and reasons for withdrawalNumber of serious adverse events (deaths and hospitalisations) by study arm

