### Safety reporting

ICH definitions of adverse events (AEs) in this study will be interpreted in light of the lack of testing for any new diagnostic or medicinal product.

We will capture untoward events occurring during the period under observation in order to understand if either approach (current practice vs. new package of interventions) might be associated with a risk to the patient’s welfare (e.g. unnecessary use of antibiotics that could cause AEs; conversely, a practice that denies a patient a treatment that was otherwise warranted).

Non-serious AEs are to be reported on the CRF. In addition, each site principal investigator will be responsible for reporting serious adverse events (SAE) to the sponsor (FIND) within 24 h as well as to the Ethics Review Committee with which they are associated, depending on the local requirements.

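### Adverse events are grouped only by care received, with no as-randomised comparison stated; if patients are reclassified and sicker than the rest, harm from the package could be diluted or masked

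*Protocol article*

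**What the plan says.** Table 5 (Populations for statistical analyses) defines the safety population as "All participants randomly assigned to trial intervention" and adds: "Participants will be analysed according to the intervention they actually received".

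The safety endpoint is a secondary outcome: "Proportion of participants experiencing adverse events (see description in Safety reporting section". The Safety reporting section says untoward events are captured "in order to understand if either approach (current practice vs. new package of interventions) might be associated with a risk to the patient’s welfare". The Data and safety monitoring board section names the harm to watch for, namely that "the diagnostic algorithm may fail to detect a need for antibiotics in some participants". The board is to see deaths and hospitalisations tabulated by study arm.

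The Interventions section describes a package of tests, algorithm, training with communication, and clinic process flow. Participant flow says the tests come on top of routine ones. Blinding and masking states that the trial is open label. Use of the algorithm is a separate secondary outcome: "Proportion of healthcare workers who adhered to new algorithm".

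**The concern.** The safety set already contains every randomised participant. The grouping sentence therefore has an effect only when the care received differs from the arm assigned, and its effect is then to move that person to the other group.

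That suits a trial in which exposure is a drug taken or not taken. Here the safety question is about two ways of managing fever. When a clinician sets the package aside after randomisation, that is part of how the package performs in use, and the reason may be how ill the patient looks. Only the comparison by assigned arm keeps such patients, and whatever happens to them, on the side of the strategy that produced them.

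At stake is the adverse-event check on a package meant to reduce prescribing. If reclassified patients were sicker than average, the package could look safer than it is. The final safety table could also group the same serious events differently from the monitoring board's table.

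**Working it through.** The article gives no adverse-event rate, departure rate or safety power, so there is no figure to reproduce. All rates below are assumptions, and they apply only if patients are in fact reclassified.

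**A. No true difference.** Assume 1,000 per arm and a 1% serious-event risk in both, so 10 against 10 events as randomised and a relative risk (RR) of 1.0. Let a share x of intervention patients, with event risk m, be counted as controls.

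- Intervention as received: (10 − 1,000·x·m) / (1,000·(1 − x))
- Control as received: (10 + 1,000·x·m) / (1,000·(1 + x))

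| x | m | Intervention | Control | RR |
|---|---|---|---|---|
| 10% | 3% | 7/900 = 0.78% | 13/1,100 = 1.18% | 0.66 |
| 5% | 3% | 8.5/950 = 0.89% | 11.5/1,050 = 1.10% | 0.82 |
| 10% | 2% | 8/900 = 0.89% | 12/1,100 = 1.09% | 0.81 to 0.82 |
| 10% | 1% | 9/900 = 1.00% | 11/1,100 = 1.00% | 1.00 |
| 0% | – | 10/1,000 | 10/1,000 | 1.00 |

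**B. True harm.** Assume risks of 2% (intervention) and 1% (control), a true difference of +1.0 percentage point. Let those moved have r times the risk of those who stay.

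- Risk in stayers: s = 2% / (1 − x + r·x)
- Control as received: (1% + x·r·s) / (1 + x)
- As-received difference: s minus that control risk. Arm size cancels.

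For x = 10% and r = 2: s = 2%/1.1 = 1.82%; control = (1% + 0.1 × 3.64%)/1.1 = 1.24%; difference = +0.58.

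| x | r = 1 | r = 2 | r = 4 |
|---|---|---|---|
| 5% | +0.95 | +0.77 | +0.46 |
| 10% | +0.91 | +0.58 | +0.07 |
| 20% | +0.83 | +0.28 | −0.42 |

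Analysed as randomised, the difference is +1.0 in every cell. The distortion is small when those moved are no sicker than the rest. It is large, and can reverse sign, when many are moved and they are much sicker.

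**C. Other analyses by arm.** The Analysis of endpoints section compares the favourable day 7 outcome, which includes survival, between arms in the mITT and PP populations. Neither is a clean as-randomised set: Table 5 words mITT as "Participants in RAI with partial data (but not fully compliant with the protocol", and PP keeps only full compliers. Table 5 also defines a population of all randomised participants, but that section assigns it no endpoint.

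**The case against.** A reader might infer that any intervention patient taken off the algorithm is counted as a control. The article does not say so, and several sections point the other way. Algorithm departure is measured as adherence, from the case report forms. Efficacy analyses and Other analyses treat compliance within arms, so non-compliant participants stay in their arm there. A patient who was tested and counselled but treated off-algorithm has plausibly received the package. The ordinary meaning of an as-received safety set is patients handled in the wrong arm by mistake. This objection stands, and it makes the risk conditional.

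The mechanism is also limited. The eligibility criteria exclude patients whose illness needs admission or referral, and Fig. 1 has a category that leaves the antibiotic to clinical judgement, so some discretion lies inside the algorithm. Both points narrow the problem without removing it.

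A reader might also infer that harm would be wholly hidden. It would not: the monitoring board sees serious events by study arm, and the day 7 outcome is compared by arm. But monitoring is not the reported comparison, and the day 7 analysis sets have the weakness shown above.

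Finally, as-received safety grouping is a common convention, and the statistical analysis plan, which is not shown, may define what counts as received. The lack of a definition would not be a finding by itself. The article does, however, fix the grouping rule, and that rule fits poorly with the stated aim of learning "if either approach (current practice vs. new package of interventions) might be associated with a risk".

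**Conclusion.** The point holds as a conditional risk. The only adverse-event grouping the article states is by care received. That is the wrong primary grouping for an open-label comparison of two care strategies, because receipt of a four-part package has no clear meaning and setting the package aside is part of the strategy's effect.

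The size is unknown. The illustrative relative risks of 0.66 to 0.82 in place of 1.0 require both that patients are moved and that those moved are sicker. If nobody is moved, there is no distortion. The documents do not support the claim that off-algorithm patients will be counted as controls. They do support replacing a rule that permits this with one that rules it out.

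**What to change.** Reword the safety row of Table 5, and carry it into the analysis plan: the primary safety analysis includes all randomised participants, each in the arm to which they were randomised. This matches the monitoring board's tabulation by study arm. Keep an as-received table as supplementary only, limited to participants handled in the wrong arm through an allocation error. State that departures from the algorithm do not change a participant's arm.

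The change is a line of wording and uses data already collected. The drawback is slight dilution of a real safety difference if the package is often not delivered.
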